### Objectives and hypotheses

The objective of our study is to assess the effectiveness of the community-based group programme TRAMPOLINE for children aged 8-12 years with at least one substance-abusing parent. The effectiveness of the intervention will be tested two weeks and six months after the intervention. We expect that as a direct result of the intervention, participants in the intervention condition will show a significant improvement in the use of constructive coping strategies (in general and within the family) compared to the control condition. We furthermore hypothesise that this effect will continue or become stronger in the 6-month follow-up data collection point (primary hypothesis). We also expect that exposure to the intervention will lead to other significant improvements in the intervention participants, especially in the area of psychological stress and addiction-related knowledge compared with the control condition (secondary hypothesis). Here also, we expect that these effects will be demonstrated directly after the intervention and in the 6-month follow-up measurement. For the parents, TRAMPOLINE offers an optional two-session accompanying programme. We will explore if these parent modules are also effective in improving caregivers' sensitivity about their children's needs within the substance-abusing family, caregivers' parenting skills, caregivers' feelings of self-competence with regard to parenting skills and caregivers' willingness to accept help from the outside. Another goal of our study is to explore the age- and gender-specific effectiveness of the programme. Given the fairly wide age range of participants and the above-mentioned gender differences in reacting to family problems, programmes like TRAMPOLINE need to be problem-specific and allow for these differences at the same time. Also we will explore regional effects such as differences in urban or rural settings on program success. We further aim at gathering more insight with exploratory analyses on characteristics of our target group, i.e. children from substance-affected families, by applying a broad battery of measurements, because this population is still vastly understudied in Germany. With regard to process evaluation, we will examine whether the intervention is delivered in time and according to defined standards, if the manual is adhered to and whether the programme meets the expectations of caregivers, parents and involved children.

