## Methods/Design

### Trial design

The effectiveness of the nine-session group programme TRAMPOLINE for children from substance-affected families will be tested in a multicentre randomised controlled trial. Out-patient counselling facilities across the nation were chosen as project facilities since they currently have primary access to the target group in Germany. In total, 27 facilities from different settings (rural/urban, Northern/Southern/Eastern/Western regions of the country) deliver interventions. The group programme TRAMPOLINE was designed and manualised in 2008/2009 during the first phase of the 3.5-year project. It is specifically geared to the issues and needs of children and parents in substance-affected families. The control condition was originally planned as a "Treatment as usual (TAU)" group, until it became clear that TAU varies strongly between facilities due to their heterogeneous approaches and is in many cases hardly comparable to a structured group programme (e.g., individual counselling sessions over many months). Thus, to ensure comparability, we designed a group programme with the same duration that is not addiction-specific (both interventions are described below) and that functions as control group setting. This will enable us to identify effects of TRAMPOLINE that go above and beyond a general group setting with effects resulting from variables such as trainer attention or social networking. We view this as quite a rigorous test, given the fact that the common design of many international studies of this kind utilises wait-list controls and thus compares "intervention" with "no intervention" [35]. At baseline N = 218 children aged 7-13 years have entered the programme. Although the programme is designed for 8 to 12 year-olds, execeptions were made after screening for children whose developmental status fits in with this age group, allowing for the occasional 7 to 13 year-old. For each project centre, our research institute randomly assigned participating children either to the intervention condition or to the control condition. At the time this manuscript is drafted, the field phase is ongoing, with baseline data collection already completed.

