### Statistical analyses

The sample size for our study is based on a power analysis for detecting small effect sizes. In general, existing literature shows that medium effect sizes can occur, but these studies utilise wait-list controls so that effects may be stronger than in the study at hand. When using a two-sided test at alpha = 0.05 and a power of (1-beta) = 0.80, a total sample of at least N = 200 is required [70]. This takes a worst case scenario of 30% loss-to-follow-up after randomisation into account. Data will be analysed in a 2 × 2 ANCOVA design and in accordance with the per-protocol principle, since we are primarily interested in the effect of the programme on those children that actually participated in the programme from start to finish. In addition, in secondary analyses we will examine the data following the intention-to-treat principle to identify possible effects of attrition. A dropout analysis will be conducted. Missing data will be imputed. The ANCOVA approach will be employed for baseline-adjusted analyses. For computations, the SPSS standards software will be used.

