## Discussion

There is a substantial need for evidence-based programmes targeting children from substance-affected families. In Germany, the research project TRAMPOLINE presented in this study protocol is the first to develop and evaluate such a programme. It is hypothesised that the addiction-specific group programme TRAMPOLINE will elicit superior effects in participating children as compared with participants in an addiction-unrelated play group on several relevant indicators such as coping skills or psychological distress. By working together with many different institutions, we also hope to gather knowledge on the implementation of such a programme, especially concerning recruitment challenges and the integration of such a programme into the standard processes of outpatient counselling centres. The study and its intervention have several strengths: First, the intervention is carefully planned and tailored to the needs of children from substance-affected families, taking into account both theoretical foundations and experience of practitioners in the field. Second, the intervention is designed to be delivered by non-therapists and is easy to deliver due to the manual and to its modular structure. Thus, we view it as a pragmatic, low-threshold programme that can be disseminated widely into different contexts. Third, there is a strict separation between programme deliverers and programme evaluators so that bias is reduced. A further reduction of bias is achieved by gathering not only child self-report data, but also the caregivers' view on children's development. Fourth, in conducting a 6-month follow-up, we are able to detect sleeper effects and test the stability of effects uncovered in the post-measurement. Fifth: we conduct a rigorous evaluation by comparing the effects of the programme with an intervention of similar dosage, but without addiction-specific content.

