The limitations of the study must also be mentioned: Due to the volatile nature of the families we target, it may be difficult to motivate them to participate in follow-up assessments. Also, many substance-affected parents will not let their children participate in the programme, thus creating a selection effect in the sample from the start. Moreover, we view the age range of the participating children as substantial and it must be seen if the programme will be beneficial for all age groups. For example, some exercises require writing and reading skills, and trainers have reported that especially younger children still need quite a lot of help in this area. Furthermore, it would be desirable to compare the effects of the programme with a naturalistic sample of children from substance-affected families not receiving any intervention. It was attempted to recruit this sample, but it quickly became clear that this recruitment challenge would exceed our resources. We also expect that attrition during the interventions will be substantial, because families view a weekly participation of their children in such a programme as a high demand on their daily routine. We try to handle this problem by encouraging our cooperating centres to contact the families if a child does not show up for a session and to support the families in any way they can regarding transportation and logistics. The reasons for dropouts are to be documented and will be analysed within the process evaluation. We hope to find out whether dropouts are due more to reasons such as time constraints in the family or rather to dissatisfaction with aspects of the programme or both. This analysis can possibly provide insights into the acceptance of the programme.

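### The primary analysis is per-protocol on programme finishers with intention-to-treat only secondary, which puts the main result of a randomised superiority trial at risk of selection bias

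*Protocol article*

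**What the plan says.** The Statistical analyses section sets the main analysis, an ANCOVA, "in accordance with the per-protocol principle, since we are primarily interested in the effect of the programme on those children that actually participated". It describes the set of interest as "those children that actually participated in the programme from start to finish". Intention-to-treat has a lesser role: "in secondary analyses we will examine the data following the intention-to-treat principle to identify possible effects of attrition". The section also announces a dropout analysis, imputation of missing data (without saying for which analysis set) and baseline adjustment by ANCOVA. Nothing elsewhere in the article makes intention-to-treat primary or co-primary.

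The trial is randomised. Under Trial design, "our research institute randomly assigned participating children either to the intervention condition or to the control condition", separately for each centre. Its hypotheses are superiority hypotheses, although that word is not used for them. Under Objectives and hypotheses, "participants in the intervention condition will show a significant improvement in the use of constructive coping strategies" relative to control, and the Discussion expects that TRAMPOLINE "will elicit superior effects in participating children as compared with participants in an addiction-unrelated play group". The Discussion also says: "We also expect that attrition during the interventions will be substantial".

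**The concern.** Whether a child stays through nine weekly sessions is known only after randomisation, and the family decides it. The two programmes also ask different things of a family. The Interventions section gives TRAMPOLINE modules on alcohol and drug problems in the family, and homework. The control manual contains play activities only, and its trainers are asked not to open addiction topics. Objectives and hypotheses describes parental substance use as a subject many families treat as taboo. A family could therefore leave one arm for a reason that does not exist in the other.

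If so, TRAMPOLINE finishers and play-group finishers are different selections of children, and part of any difference in coping between them reflects who stayed. Interest in children who take part is legitimate, but this comparison does not in general answer it: the control children who would have finished TRAMPOLINE are not identified. The choice also sits badly with the Discussion's description of a pragmatic programme for wide dissemination, because that question includes children who stop.

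**Working it through.** **Inputs from the article.** Two-sided alpha 0.05; power 0.80; planned N = 200 including 30% loss to follow-up, which leaves 200 × 0.7 = 140, or 70 per arm if allocation is equal (the ratio is not stated); 218 enrolled. Neither finishing rates nor differences between finishers and non-finishers are given, so those below are assumptions.

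**The plan's own figure.** The small effect behind N = 200 has no number, so N = 200 cannot be uniquely reproduced. A standardised difference of 0.2 would need 786, or 1,123 with 30% loss. An unadjusted comparison of 140 children detects about 0.47 with 80% power. The present point does not depend on this.

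**Bias formula.** Let p be the share finishing and δ the finisher-minus-non-finisher difference in outcome, in SD units. An arm's finisher mean exceeds its full mean by (1 − p)δ. With no true effect, the finisher comparison is off by

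bias = (1 − pI)δI − (1 − pC)δC (I = TRAMPOLINE, C = control).

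| Assumed pattern | Bias (SD) |
|---|---|
| Same p and same δ in both arms | 0 |
| 70% vs 85% finishing, δ = 0.5 in both | 0.3 × 0.5 − 0.15 × 0.5 = 0.075 |
| 70% finishing in both, δI = 0.6, δC = 0 | 0.3 × 0.6 − 0 = 0.18 |
| 70% finishing in both, δI = −0.6, δC = 0 | −0.18 |

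**False-positive rate, unadjusted, 70 per arm.** The test statistic shifts by bias × √(70/2) = bias × 5.92.
- 0.075 × 5.92 = 0.44: rejection about 7%.
- 0.18 × 5.92 = 1.07: rejection about 18%.

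**Effect of the planned baseline adjustment.** Assume a baseline–outcome correlation of 0.5, so the residual SD is √(1 − 0.25) = 0.866.
- If the 0.18 SD difference is equally present at baseline, 0.18 − 0.5 × 0.18 = 0.09 remains. The shift is 0.09 × 5.92 / 0.866 = 0.61: rejection about 9%.
- If the selection is unrelated to the baseline score, the full 0.18 remains. The shift is 0.18 × 5.92 / 0.866 = 1.23: rejection about 23%. Adjustment then removes no bias and, by shrinking the residual SD, makes false rejection more likely.

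**Simulation of a finishers-only, baseline-adjusted ANCOVA with no true effect** (109 per arm, baseline correlation 0.5, selection on the part of the outcome that baseline does not explain, 6,000 runs per scenario).
- 30% dropout in each arm with the same selection: rejection about 5%.
- 40% vs 20% dropout with the same selection (latent correlation 0.3 to 0.5): bias 0.08 to 0.12 SD, rejection 8% to 16%.
- 30% in each arm, with only TRAMPOLINE dropout related to outcome (latent correlation 0.3 to 0.5): bias 0.13 to 0.22 SD, rejection 17% to 35%.

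**Power after the change.** Assume d = 0.40 in completers, no gain in children who stop, everyone followed up, N = 218, unadjusted. The intention-to-treat effect is completion share × 0.40.

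| Completion | Effect, all randomised | Power, all randomised | Power, finishers only, if unbiased |
|---|---|---|---|
| 100% | 0.40 | 84% | 84% |
| 90% | 0.36 | 76% | 80% (218 × 0.9 = 196 children) |
| 80% | 0.32 | 66% | 75% (174 children) |
| 70% | 0.28 | 54% | 70% (153 children) |

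The last column uses power = Φ(0.40 × √(n/2) − 1.96), with n finishers per arm.

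**The case against.** The plan states its choice and its reason openly, and it already includes an intention-to-treat analysis and a dropout analysis, so a discrepancy between the two results would be visible. The only cause the Discussion asserts for the expected attrition is the burden of weekly attendance. Both arms share that burden: the control takes the same time, and the groups were described to families as equally attractive. Similar attrition in both arms is therefore a real possibility, and the bias could be nil.

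All of this stands, and it limits the claim to a risk. It does not remove the risk, because similar attrition is hoped for and cannot be guaranteed, and a dropout analysis describes selection without undoing it. When the two analyses disagree, the plan makes the finisher result the primary one.

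A reader might infer several stronger points that the documents do not support:
- **The bias favours TRAMPOLINE.** Nothing in the article fixes its direction.
- **Families leave because they dislike the programme.** The Discussion only asks whether dissatisfaction plays a part.
- **The per-protocol set must fall below the planned size.** At 70% finishing, 218 × 0.7 = 153, above 140. A shortfall needs fewer than 140/218 = 64% to be analysed.
- **Imputation has nothing to do among finishers.** A child can finish the programme and still miss an interview, and the imputation sentence is not tied to one analysis set.
- **Only children with perfect attendance count.** Taking part from start to finish can equally mean not dropping out.

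**Conclusion.** The concern holds as a risk of selection bias in the primary result. The ranking of the two analyses is stated plainly in the article and is not a detail left to an unseen analysis plan. Baseline ANCOVA, the dropout analysis and imputation do not restore the randomised comparison among finishers.

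Size and direction are unknown. The two illustrative positive patterns, 0.075 and 0.18 SD, rest on assumed finishing rates and differences, and the larger needs selection in one arm only. They do not bound the bias: zero and negative values are equally compatible with the documents. A bias of that order would still matter in a trial that says it is powered for small effects.

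**What to change.** In Statistical analyses, make the primary analysis that of all randomised children in their assigned arm. State that the t1 and t2 interviews are sought whatever the attendance. Handle missing outcomes by multiple imputation or a likelihood-based mixed model that includes the baseline score. Keep per-protocol as a supportive analysis, with an attendance definition fixed before the outcome data are examined. A complier-average estimate is optional at most and must state its assumptions: no effect of assignment in non-compliers is doubtful with an active control and an attendance threshold.

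The analytic cost is small, since both analyses are already planned and interviewers visit families at all three time points. The article does not say whether children who leave the programme are still visited, so this may need a field instruction and some extra visits. At drafting, fieldwork was still under way, with only baseline collection complete.

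The statistical cost is dilution by children who stop. Compared with an unbiased finisher analysis under the same assumptions, power would fall from about 80% to 76% at 90% completion, and from about 70% to 54% at 70% completion. The stated power should be rechecked and restated for the new primary analysis, with a numeric effect size.

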## Background

The negative impact of parental substance use on children has been documented by a multitude of studies and reviews, especially for children of alcoholics. It includes physical, psychological and cognitive consequences for children's development. Children and adolescents affected by parental drug use show higher rates of externalizing and internalizing problems such as anxiety disorders and depression [1,2], social behaviour disorders [3,4], or hyperactivity disorders [4,5]. With regard to substance use problems, their records more often show an early onset of substance consumption [6,7], earlier drunkenness experiences [8], increased binge drinking rates [9] and an elevated risk for developing substance use disorders at a younger age than comparable peers [10]. Approximately 33 to 40 percent of all children with a substance-using parent will develop a substance use disorder themselves [11]. Substance problems are transmitted to the next generation via several pathways, especially genetic disposition [12,13], exposure to drugs in utero, behavioral and cognitive processes [14,15]. Family environmental characteristics such as problematic family relationships, family conflict or absence of supportive parenting [16] also play an important part. Children from substance-affected families often experience physical violence, emotional abuse, or neglect [17]. Paradoxically, at the same time they often acquire the same positive expectations about the effects of substance consumption that their substance-abusing parent exhibits [18,19]. Learning from the example substance-dependent parents set, children later come to use substances as maladaptive coping strategy in stressful and difficult times [20-22]. Behavioural consequences in childhood and adolescence are gender-specific: while females lean toward withdrawal and social isolation, males often show antisocial behaviour [17]. In general, male children seem to have more difficulties with compensating for family problems resulting from parental alcohol or drug use. They more often develop attention deficit problems, anxiety, depression and early alcohol problems [23]. However, not all children from substance-affected homes show maladaptive functioning. In fact, about one third of them exhibit no psychosocial problems in spite of the adverse circumstances associated with parental substance use [24,25]. These persons are often called "resilient".

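### Age and sex could be prespecified as covariates beside the baseline score in the primary ANCOVA: a small gain at almost no cost

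*Protocol article*

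**What the plan says.** All places are in the protocol article.

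- **Statistical analyses.** The primary analysis is a 2 × 2 ANCOVA in children who completed the programme. The only adjustment named is in the sentence "The ANCOVA approach will be employed for baseline-adjusted analyses". The two factors of the 2 × 2 layout are not identified. Intention to treat is secondary, and a dropout analysis and imputation are announced.
- **Trial design.** 218 children aged 7 to 13 entered. Allocation was random within each centre; no balancing on age or sex is described.
- **Background.** On sex: "In general, male children seem to have more difficulties with compensating for family problems".
- **Objectives and hypotheses.** "Another goal of our study is to explore the age- and gender-specific effectiveness of the programme".
- **Discussion, limitations.** On age: "we view the age range of the participating children as substantial". On exercises that need reading and writing, trainers report that "especially younger children still need quite a lot of help in this area".
- **Data collection and Table 1.** Socio-demographic data are collected from children and parents. The items are not listed, but age is an inclusion criterion.

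**The concern.** The authors expect children of different age and sex to differ, and the variables should already be in the data set, but the one stated adjustment does not use them. Two things are at stake.

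The first is precision. A covariate that predicts the outcome beyond the baseline score narrows the interval for the treatment effect.

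The second concerns the primary analysis set. It keeps only children who finished, so randomisation no longer guarantees equal age distributions in the two arms being compared. TRAMPOLINE contains reading and writing exercises, while the Interventions section describes the control as drawing, crafts, exercise and games. An age-related burden could therefore fall on one arm. If it affected completion, finishers would differ in age between arms, and an analysis without age would carry that difference into the treatment contrast.

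**Working it through.** **The plan's own figure.** The article states "The sample size for our study is based on a power analysis for detecting small effect sizes", with a "two-sided test at alpha = 0.05 and a power of (1-beta) = 0.80", and concludes that "a total sample of at least N = 200 is required" after allowing for 30% loss. It gives no numerical effect, SD or baseline correlation, so 200 cannot be rebuilt uniquely. That is a separate matter. Here the figure only sets a power scale: 200 × 0.70 = 140 analysed, 70 per arm, and the standardised difference detectable with 80% power is (1.960 + 0.842) × √(2/70) = 0.474.

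**Precision.** Let R² be the share of post-baseline variance explained by age and sex. It is not in the article; 2 to 10% is assumed.

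- Standard error ratio = √(1 − R²).
- Equivalent extra children = n/(1 − R²) − n, with n = 218 × 0.70 = 152.6. The 30% is the plan's worst case for loss to follow-up; the per-protocol set could be smaller.
- Power on the scale above = Φ(2.802/√(1 − R²) − 1.960).

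| R² | SE ratio | SE reduction | Extra children | Power (80% without) |
|---|---|---|---|---|
| 0.02 | 0.990 | 1.0% | 3.1 | 80.8% |
| 0.05 | 0.975 | 2.5% | 8.0 | 82.0% |
| 0.10 | 0.949 | 5.1% | 17.0 | 84.0% |

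Estimating two further coefficients inflates the standard error by about √(1 + 2/153) = 1.007. The net reductions are therefore nearer 0.4%, 1.9% and 4.5%. At R² = 0 there is no gain and a very slight loss.

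**Age imbalance among finishers.** The article gives no completion rates by age, so every input here is assumed. True effect is 0, completion is 70% at mean age, and the outcome slope is 0.1 to 0.3 SD per SD of age (0.3² = 9% of variance, within the 10% cap above). The odds of completing rise by 1.5 or 2 per SD of age. To first order, the mean age of finishers shifts by ln(OR) × (1 − 0.70) SD, and the bias is that shift times the slope:

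- OR 1.5 in TRAMPOLINE only: shift 0.405 × 0.30 = 0.122 SD of age; bias 0.012 to 0.036 SD. Simulation: 0.013 to 0.038.
- OR 2 in TRAMPOLINE only: shift 0.693 × 0.30 = 0.208 SD of age; bias 0.021 to 0.062 SD. Simulation: 0.020 to 0.061.
- The same OR in both arms: the shifts cancel. Simulated bias is at most about 0.003 SD, which is noise.
- With age in the model, the one-arm scenarios also fall to within about 0.003 SD of zero.

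A cruder scenario gives the same order of size. Suppose 50% of children aged 9 or under and 85% of older ones finish TRAMPOLINE, with no age trend in control. Under an assumed age distribution with SD 1.57 years, finishers differ by about 0.33 years. The steepest slope compatible with 10% of variance is √0.10/1.57 = 0.20 SD per year, so the bias is 0.33 × 0.20 = 0.066 SD.

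**The case against.** The strongest reply is that a condensed article need not list covariates. A fuller list may stand in a document not shown, and the baseline adjustment is not expressly limited to the baseline outcome score. This stands: the omission is not an error, and nothing in the section is contradictory. What remains is an improvement to the one adjustment that is stated.

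A second reply is that the age and sex statements mostly concern who benefits, which is effect modification, and this does not establish prognostic value for coping once the baseline score is in the model. That also largely stands. The Background sentence on boys is a main-effect statement, but about other problems, not coping given baseline. The gain is therefore shown as a range that includes zero.

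Three stronger readings are tempting, and the article does not support them.

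- **A reader might infer that younger children drop out of TRAMPOLINE more often, so that the primary contrast is biased.** The Discussion says they need help, not that they leave. It mainly attributes expected attrition to the weekly demand on family routine. Delivery is described as age-based, and 7- and 13-year-olds enter only after screening for developmental fit. Dissatisfaction with the programme is left open as a cause of dropout, so age-related completion is possible but undocumented. It biases the contrast only if it differs by arm.
- **A reader might infer that any such selection goes unexamined, or that the age question is answered only in finishers.** Intention to treat, a dropout analysis and imputation are planned, although they do not repair a per-protocol primary result. Nothing confines the age and gender exploration to finishers.
- **A reader might take a slope of 0.3 SD per year and reach a bias of 0.10 SD.** With an age SD of 1.57, that slope implies (0.3 × 1.57)² = 22% of variance from age alone, which contradicts the 10% cap used for precision.

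Chance age imbalance at randomisation is not bias either; the standard error already reflects it.

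**Conclusion.** The point holds as a low-severity improvement. Baseline is the only adjustment stated, while the protocol itself names age and sex as sources of heterogeneity.

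Adding them would cut the standard error by about 1 to 5% if they explain 2 to 10% of post-baseline variance, slightly less after the cost of two more coefficients, and not at all if they explain nothing. It would also guard the finishers-only contrast against an age imbalance that would arise if completion depended on age in one arm only. The resulting bias would be up to about 0.06 SD under the assumed ranges (0.066 in the cruder scenario).

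Both figures rest on assumptions, not on data in the article. Age adjustment would not remove selection through family circumstances, which is the article's main expected reason for attrition. The choice of a per-protocol primary set is the weightier matter and is not resolved here.

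**What to change.** State in the analysis section that the t1 and t2 ANCOVA models include the baseline score, age at programme start (continuous) and sex, in both the per-protocol and the intention-to-treat analysis. State also that the exploratory age-by-arm and sex-by-arm interactions are tested in all randomised children, and that completion rates are tabulated by age and arm beside them. If a fuller analysis plan already lists these covariates, a cross-reference is enough.

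The cost is a sentence or two, two degrees of freedom in the main models, and no new data, provided the socio-demographic items include age and sex, as one would expect. The article says that the field phase was still under way, so the covariates could be fixed before the outcome analysis.
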